**1. Summary**

*Background*

An estimated 24 million people worldwide have dementia, the majority of whom are thought to have Alzheimer’s disease (AD). AD is characterized by extracellular parenchymal and vascular amyloid deposits comprising amyloid β protein (Aβ) and the neurofibrillary tangle formed by microtubule-associated protein tau.

Rosmarinic acid (RA) is an ester of caffeic acid and 3,4-dihydroxiphenyllactic acid. It has several interesting biological activities, e.g., antioxidant, anti-inflammatory, antimutagen, antibacterial, and antiviral [1]. We previously reported that RA dose-dependently inhibited Aβ fibrils formation from Aβ_40_ and Aβ_42_, as well as destabilizing preformed Aβ fibrils *in vitro* [2]. Recently, we showed that RA inhibited both Aβ_40_ and Aβ_42_ oligomerizations *in vitro* [3]. Pharmacokinetics profiles containing food effects of *M. officinalis* extract including RA have not been reported.

*Objectives*

The objective of this study was to evaluate the pharmacokinetics including food-effect and safety of *M. officinalis* extract containing 500mg, 250mg and 100mg of RA in healthy individuals.

*Methods*

Participants will be randomly assigned to treatment arms in the two studies [Study 1 (fasted state) and Study 2 (fed state)].

**2. Eligibility**

Healthy volunteers will be recruited through flyers posted on Kanazawa University notice boards. Participants will complete a detailed questionnaire that is developed to collect demographic, health, and dietary information. Eligible participants in the study included both males and females who are aged above 20 years. Individuals are excluded if they have (i) a disease condition, such as dementia or liver, renal, or heart dysfunction; (ii) a history of cancer; (iii) allergies to polyphenols or any drug or food ingredient; or (iv) consumed any supplement containing rosmarinic acid within 15 days of the first RA administration. Furthermore, women are excluded if they were pregnant or lactating.

**3. Target sample size**: We chose the sample size (n=9~18) to assess the primary objective of pharmacokinetics of RA.

**4. Methods**

This is a placebo-controlled trial to investigate the safety, tolerability and pharmacokinetics of RA.

**5. Study design**

5.1. Study 1 (fasted state)

Each participant will receive three separate interventions (investigation #1, #2, and #3) designed by groups A, B, or C in a 3 × 3 Latin square design with the order of consumption randomized and separated by a ten-day interval (wash-out period) (Figure 1). In details participants who allocated to group A are applied placebo in the investigation #1, and are applied RA 250 mg in the investigation #2 and are applied RA 100 mg in the investigation #3. Similarly, group B is applied RA 250 mg, placebo and RA 500 mg in the investigations #1, #2, and #3 respectively. Group C is applied RA 100 mg, RA 500 mg and placebo in these investigations #1, #2, and #3 in order given (Figure 1). Each intervention is conducted for 10 days, consisting of a 7-day controlled diet period and a 3-day intervention period. In order to avoid the effects of polyphenols derived from other food sources during the intervention and controlled diet periods, participants are asked to consume foods that contain minimal amounts of polyphenols, such as rice and fish. The participants will fast for 12 h before the administration of RA or placebo.

Figure 1.

[figure not shown]

5.2. Study 2 (fed state)

In this fed state arm, placebo or RA will be administered 30 min after completion of the standardized low-polyphenol meal, i.e. rice ball and clear soup. The other procedures of Study 2 will be carried out in the same procedure as in the Study 1.

5.3. Polyphenol rich foods list

5.3.1. Rosmarinic acid rich foods

Lemon balm (*Melissa officinalis L.*), Rosemary (*Rosmarinus officinalis L.*), Perilla (*Perilla frutescens L.*), Sage (*Salvia officinalis L.*), Lavender (*Lavandula officinalis L.*), Tyme (*Thymus vulgaris L.*)

5.3.2 Polyphenol rich foods list (1)

Red wine, Beer, Green tea, Coffee, Cocoa, Chocolate, Black tea, Curry.

5.3.3. Polyphenol rich foods list (2)

Buckwheat, Soy, Eggplant, Onion, Broccoli, Grape, Strawberry, Apple, Raspberry, Olive, Sesame.

5.4 Placebo and RA capsules

5.4.1 Rosmarinic acid

Chemical name: Rosmarinic acid

Stractural diagram:

[figure not shown]

Molecular weight: 360.0845

Molecular formula: C_18_H_16_O_8_

RA capsules are provided free from Maruzen Pharmaceuticals Co., Ltd., Japan. Each RA capsule contained 185 mg *M. officinalis* extract along with 50 mg RA, 60 mg lactose, and 5 mg calcium sterate.

5.4.2 Placebo

Placebo capsules are provided free from Maruzen Pharmaceuticals Co., Ltd., Japan. Each placebo capsule contained 210 mg lactose, 35 mg caramel, and 5 mg calcium stearate. There is no detectable RA content in the placebo capsule.

5.5 Random allocation

The study statistician generate the random allocation sequence. All subjects will be randomly allocated to treatment arms.

5.6 Study methods

5.6.1 Study 1 (fasted state)

Group A: Placebo (intervention #1) - Rosmarinic acid 250 mg (intervention #2) – Rosmarinic acid 100 mg (intervention #3)

Group B: Rosmarinic acid 250 mg (intervention #1) - Placebo (intervention #2) – Rosmarinic acid 500 mg (intervention #3)

Group C: Rosmarinic acid 100 mg (intervention #1) - Rosmarinic acid 500 mg (intervention #2) – Placebo (intervention #3)

5.6.2 Study 2 (fed state)

Group D: Placebo (intervention #4) - Rosmarinic acid 250 mg (intervention #5) – Rosmarinic acid 100 mg (intervention #6)

Group E: Rosmarinic acid 250 mg (intervention #4) - Placebo (intervention #5) – Rosmarinic acid 500 mg (intervention #6)

Group F: Rosmarinic acid 100 mg (intervention #4) - Rosmarinic acid 500 mg (intervention #5) – Placebo (intervention #6)

5.7 Dosage of RA

To date, the safety dosage of RA has not yet been investigated in humans. It has been reported that M. officinalis extract, at a dose of 60 drops/day (500 μg citral /ml, presumably contains 240 mg RA) for 16 weeks, produced a significantly better outcome on cognitive function in patients with mild to moderate AD [4].

Acceptable daily intake (ADI) is a measure of the amount of a specific substance in food that can be orally ingested on daily basis over a lifetime without appreciable health risk [4]. An ADI value can be calculated from the no-observed-adverse-effect level (NOAEL) dividing by one hundred [5]. In our study using AD model transgenic mice (Tg2576), RA exhibited no adverse effect considered drug-related at a NOAEL of 1g/ kg BW/ day in the 10 months study [3]. When human body weight was assumed to be 50 kg, NOAEL was determined 50 g per day. Then, the ADI value of RA was calculated 500 mg per day.

5.7 Prohibited medications, supplements and other substances

The subjects has received any of the treatments about rosmarinic acid other than this trial or supplements contains polyphenol.

It was reported that lemon balm might induce depression in patient who undergo surgery by general anesthesia [6]. In case of general anesthesia, test schedule must be discontinued. It has been reported *M. officinalis* extract have sedative effects [7][8]. There is some possibility that *M officinalis* extract causes drowsiness. The combination use with sleep inducing drug or antianxiety drug and test capsule (rosmarinic acid or placebo) must be careful enough.

**6. The absorption and metabolic properties of Rosmarinic acid**

The previous study reported that the concentration of intact and conjugated RA in the plasma were at most ~20 nmol/L and ~1200 nmol/L 0.5 h after administration of a single dose of 200 mg RA, respectively [9].

**7. Test Schedule**

7.1.1 Physical condition and subjective symptoms

Physicians will interview the participants, and perform clinical and physical examinations during their visits. They will assess the subjects’ physical condition and subjective symptoms and determine whether any adverse events are experienced. The health status of each subject is examined during physical examination. The examination parameters for the trial included height, weight, body mass index, and blood pressure, which are recorded from the subjects’ brachial region while they are seated.

7.1.2 Blood tests

Laboratory blood chemistry parameters, including a hematology (white blood cell count, red blood cell count, hemoglobin levels, and hematocrit and platelet count) and blood biochemistry [levels of aspirate aminotransferase (AST), alanine aminotransferase (ALT), lactate dehydrogenase (LDH), γ-glutamyltransferase (γ-GTP), total bilirubin (T-Bil), blood urea nitrogen (BUN), and creatinine (Cr)], will be assessed with blood samples obtained at baseline and 48 h after the intake of RA or placebo. All the samples will be processed and analyzed in a laboratory (SRL. Inc, Tokyo, Japan). Baseline blood samples will be collected from the intermediate cubital vein after the subjects had fasted for 12 h, followed by further samples being collected 0.25, 0.5, 1, 2, 3, 6, 24, 48 h after intake of RA or placebo. Serum RA concentration is measured in Takasaki University of Health and Welfare (Gunma, Japan).

7.2 Adverse events

In the course of the clinical trial, adverse events associated with the study agents will be self-reported by the participants, and blood analyses including blood cell counts and blood chemical parameters are monitored. All observed and self-reported adverse events, regardless of suspected causal relationship to the study treatments, are recorded on the case report form (CRF) throughout the study.

7.3 Test schedule

7.3.1 Study 1 (fasted state)

7.3.2 Study 2 (fed state)

**8. Discontinued criteria**

A subject may withdraw (or be withdrawn) from the study prematurely for the following

reasons; (i) subject voluntarily discontinues participation in the study (consent withdrawal), (ii) unacceptable adverse events, (iii) other (must be specified).

**9. Adverse events**

9.1 Definition of Adverse Events (AE)

An AE is any untoward medical occurrence in a clinical investigation subject, temporally associated with the use of a medicinal product, whether or not considered related to the medicinal product.

9.2. Definition of Severe adverse events (SAE)

An SAE is any untoward medical occurrence that, at any dose: (i) Results in death, (ii) Is life-threatening, (iii) Requires hospitalization or prolongation of existing hospitalization, (iv) Results in disability/incapacity

9.3 Monitoring AEs

Subjects will be questioned and/or examined by the investigator for evidence of AEs. The questioning of subjects with regard to the possible occurrence of adverse events will be generalized such as, “How have you been feeling since your last visit?” The presence or absence of specific AEs should not be elicited from subjects.

9.4 Record of AEs

AEs, actions taken as a result of AEs, and follow-up results must be recorded in the CRF.

9.5 AEs after the clinical trial

If SAEs including death is any untoward medical occurrence in a clinical investigation subject after the clinical trial, the investigator will report the secretariat.

9.6 Expedited reporting

Any occurrence of SAEs in a subject in the trial must be reported expeditiously to the Kanazawa University Medical Ethics Review Board.

**10. Assessment**

10.1 Primary Endpoint

The primary outcome is to investigate pharmacokinetics of RA (M. officinalis extract) including food-effect in human.

10.2 Secondary Endpoint

The secondary outcomes are to evaluate the safety and tolerability of RA.

**11. Data analysis and statistical considerations**

11.1 Primary outcomes (Pharmacokinetics)

The maximum serum concentration (C_max_), and time at which the maximum serum concentration was observed (T_max_) will be determined from individual serum pharmacokinetic curves. AUC calculates it using trapezolital rule, expressed in mean± standard errors according to dose group (100 mg/ 250 mg/ 500 mg RA and placebo). We will compare Study 1 (fasted state) and Study 2 (fed state) of pharmacokinetics.

11.2 Secondary outcomes

In the safety evaluation, AEs compared between dose groups. Fisher’s exact test will be used to determine the significance of any differences among the 100 mg, 250 mg, 500 mg RA, and placebo groups.

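### The only stated safety analysis is a four-group Fisher test in a study sized for pharmacokinetics, and its p-value says little about which adverse event rates the data exclude

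*Protocol*

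**What the plan says.** Protocol section 10.2 sets the secondary objective: "The secondary outcomes are to evaluate the safety and tolerability of RA". Section 11.2 gives the analysis in two sentences: "In the safety evaluation, AEs compared between dose groups", and then "Fisher’s exact test will be used to determine the significance of any differences among the 100 mg, 250 mg, 500 mg RA, and placebo groups". No alpha, margin, interval or bound is attached. Section 11.1, by comparison, does name a summary for the pharmacokinetic outcome (mean with standard error by dose).

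The size of the trial comes from section 3: "We chose the sample size (n=9~18) to assess the primary objective of pharmacokinetics of RA". The protocol does not say whether this range is per study or the total over Study 1 (fasted) and Study 2 (fed), or whether AEs from the two studies are pooled.

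On prior knowledge, section 5.7 (Dosage of RA) states: "To date, the safety dosage of RA has not yet been investigated in humans".

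**The concern.** The objective is to evaluate safety and tolerability. The method named for it answers a narrower question: whether AE proportions differ significantly among four groups. In small groups that test can easily miss a sizeable excess at one dose. When it does not reject, the p-value does not tell the reader how high the AE rate could still be. An estimate with an upper bound gives that directly.

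The point matters because the protocol itself says that the safe human dosage has not been investigated, so readers will look to this trial for tolerability information. A bare non-significant p-value is weak information when it is also a likely result under a substantial harm.

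**Working it through.** **No figure to reproduce.** The protocol gives no calculation behind 9 to 18, and no alpha or power for safety.

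**Exposure counts (sections 5.6.1 and 5.6.2).** The three sequences of Study 1 are A (placebo, 250, 100 mg), B (250 mg, placebo, 500 mg) and C (100, 500 mg, placebo). Study 2 repeats the pattern as D, E and F. Placebo is in all three sequences and each dose in two of three. With equal groups and N participants in a study:
- placebo N, each dose 2N/3
- N = 9: 9 / 6 / 6 / 6
- N = 18: 18 / 12 / 12 / 12

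**Assumptions, none of them in the protocol.** The range 9 to 18 is per study; AEs are not pooled across studies; alpha is two-sided 0.05; exposures are independent, although each person is in three of the four groups; the true AE rate at 500 mg is 30%; placebo, 100 mg and 250 mg share one background rate, varied from 0% to 10%.

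**What the test needs in order to reject.** The four-group Fisher p-value sums the probabilities of all tables, at the same total number of events, that are no more likely than the one observed. With all events at 500 mg, the equally likely tables are those with all events at any one of the three doses:
- N = 9, 2 of 6: 3 × C(6,2) / C(27,2) = 45/351 = 0.128, not significant
- N = 9, 3 of 6: 3 × C(6,3) / C(27,3) = 60/2925 = 0.021, significant
- N = 18, 2 of 12: 3 × C(12,2) / C(54,2) = 198/1431 = 0.138, not significant
- N = 18, 3 of 12: 3 × C(12,3) / C(54,3) = 660/24804 = 0.027, significant

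So with 9 participants, a third of those given 500 mg could have an AE, with none elsewhere, and the test would not reject.

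**Power with no background AEs.** It is the chance of at least 3 events at 500 mg:
- N = 9: 1 − (0.118 + 0.303 + 0.324) = 0.256
- N = 18: 1 − (0.014 + 0.071 + 0.168) = 0.747

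**Power with background AEs.** Full enumeration of the four independent binomials gives:

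| Background | N = 9: power | N = 9: non-significant | N = 18: power | N = 18: non-significant |
|---|---|---|---|---|
| 0% | 26% | 74% | 75% | 25% |
| 2% | 22% | 78% | 58% | 42% |
| 5% | 18% | 82% | 41% | 59% |
| 10% | 12% | 88% | 24% | 76% |

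**Other readings of 9 to 18.** If 18 is the total and is split evenly, each study has 9 and the N = 9 columns apply. If each study enrols 18 and AEs are pooled (36 / 24 / 24 / 24), the same enumeration gives four-group power of 99%, 92%, 76% and 46% at backgrounds of 0%, 2%, 5% and 10%.

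**What an upper bound would show.** After zero events in n people the exact one-sided 95% bound is 1 − 0.05^(1/n):
- n = 6: 1 − 0.05^(1/6) = 0.393
- n = 12: 1 − 0.05^(1/12) = 0.221

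These are best cases. Under a true 30% rate, zero events at 500 mg has probability 0.7^6 = 12% or 0.7^12 = 1.4%.

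**The case against.** Several objections have force.

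- **Low power does not hold over the whole range.** With 18 participants and no background AEs the test detects a 30% rate 75% of the time, and at 2% background 58%. A reader might infer that a non-significant result is likely anywhere from 9 to 18 participants. The protocol gives no background rate, so that is not supported; the statement needs its conditions.
- **Non-significant is not event-free.** A reader might picture a clean safety table. Under a 30% rate, events at 500 mg would usually be seen: the chance of none is 12% with 6 exposed and 1.4% with 12.
- **The protocol never equates non-significance with safety.** One might infer that any safety statement could rest only on failing to reject. The documents do not support this. Sections 7.1 and 7.2 also provide for physician examination, blood tests at baseline and 48 h, and recording of all AEs, and comparing AEs between dose groups does not rule out tabulating them.
- **Some prior human data are cited.** Section 5.7 mentions a 16-week trial at presumably 240 mg RA, and section 6 a 200 mg single-dose study, so this trial is not the only human evidence.
- **Intervals and tabulations are often left to an SAP**, which is not at hand, and safety is openly secondary.

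The last point limits the weight of the finding but does not remove it. The protocol does not leave the method open: it names a significance test, and for this question at this size estimation is the better choice.

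**Conclusion.** The point holds in a limited form. The protocol fixes a significance test as its only stated safety analysis, in a study sized for another purpose, and the p-value says little about which AE rates the data exclude. With 9 participants per study the test would probably miss a 30% rate at 500 mg at every background rate examined. With 18 it would probably do so only from about 5% background upwards, and pooling two studies of 18 would raise power further. These figures rest on the assumed AE rates, equal sequence groups, the per-study unpooled reading and independent exposures. The case for estimation does not depend on any one scenario: even zero events among 12 people leaves rates up to 22% open, and a p-value does not show that. This is an inexpensive improvement to a secondary analysis; the pharmacokinetic analysis is unaffected.

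**What to change.** Rewrite section 11.2 so that estimation is the safety analysis:

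1. For each dose and for placebo, report the number and proportion of participants with at least one AE, with an exact (Clopper-Pearson) one-sided 95% upper bound. State whether this is done per study or pooled, because the denominators depend on it.
2. For each dose, report the within-participant (paired) difference from placebo with a 95% confidence interval. Pairing is possible and needed because everyone given a dose also receives placebo.
3. Keep any test as descriptive only.
4. Add a sentence such as: A non-significant test will not be interpreted as evidence of safety; the conclusion will state the largest AE rate with which the data are compatible.

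The cost is a wording change and a few more lines of analysis, with no additional participants, visits or samples. The downside is a less favourable safety statement: even after zero events it would have to say that rates up to 39% (6 exposed) or 22% (12 exposed) are not excluded.

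### Section 11.2 applies Fisher's exact test to dose groups that are overlapping sets of the same crossover participants, so its independence assumption fails and its p-values are conservative if adverse events cluster within persons

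*Protocol*

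**What the plan says.** Safety and tolerability form the secondary endpoint (Protocol 10.2). Section 11.2 gives its analysis in two sentences: "AEs compared between dose groups", and a Fisher "exact test will be used to determine the significance of any differences among the 100 mg, 250 mg, 500 mg RA", with placebo as the fourth group. It mentions no pairing, no stratification by participant and no period term.

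The design section describes a crossover. In 5.1, "Each participant will receive three separate interventions". Section 5.6.1 lists the sequences for the fasted study, here in order of period:

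- A: placebo, then 250 mg, then 100 mg
- B: 250 mg first, placebo second, 500 mg last
- C: 100 mg first, 500 mg second, placebo last

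Section 5.6.2 repeats the same three sequences as groups D, E and F for the fed study. The target sample size (section 3) is 9 to 18, chosen for pharmacokinetics. The Protocol does not say whether this is per study or in total.

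**The concern.** The randomised groups, A to F, are sequences. The four groups compared in 11.2 are treatments received, and the same people sit in several of them. Fisher's exact test takes every entry in the table as an independent unit. Someone who tends to report symptoms contributes to three columns, and the test cannot separate that tendency from an effect of dose. It also discards the comparison of each person with himself or herself, which is the main strength of the design.

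Clustering within persons is plausible here. AEs are self-reported (7.2), they are elicited by a general question about well-being (9.3), and the anticipated effect is drowsiness (13.2). If AEs do cluster, the test becomes conservative and may miss a dose-related AE. Section 5.7 on dosage says that a safe dose has not yet been studied in humans, so a missed signal is the error that matters more.

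**Working it through.** **1. Who is in each column.** Inputs: the sequences in 5.6.1, with equal allocation of N/3 per sequence (assumed). Placebo occurs in all three sequences, 100 mg in A and C, 250 mg in A and B, 500 mg in B and C.

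- Placebo: N exposures. Each dose: 2 × N/3. Total: N + 3 × 2N/3 = 3N.
- N = 9: 9, 6, 6, 6, total 27.
- N = 18: 18, 12, 12, 12, total 54.

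Every person in a dose column is also in the placebo column. No reading of 11.2 makes the four columns different people.

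**2. What ignoring the pairing does in one table.** At N = 18, 12 people receive both placebo and 500 mg. Suppose 6 have an AE on 500 mg only and none on placebo only. The exact McNemar p-value is 2 × 0.5^6 = 0.031, however many people have an AE on both. The Fisher p-value for the same 12 people is 0.014 if 0 or 6 have an AE on both, and 0.036 if 2 or 4 do. It moves with information that says nothing about the difference, and can fall on either side of the paired value.

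**3. Type I error.** The Protocol states no error rate or power to reproduce, so these are simulations on assumptions: two-sided 5%; logit P(AE) = b + treatment effect + person effect, with the person effect normal with the SD shown; b = −0.5, so about 38 to 44% of exposures have an AE. The planned test is Fisher's test on the pooled 4 × 2 table. Ranges cover repeated, separately coded simulations.

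| Person SD (logit) | n = 9 | n = 18 |
|---|---|---|
| 0 (no clustering) | 4.5–4.7% | 4.6–5.3% |
| 1.5 | 2.3–2.4% | 2.2–2.6% |
| 3 | 0.9–1.1% | 0.9–1.2% |

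**4. Power for a common, graded AE.** SD 2, b = −1.5, log-odds rising by 1 per step from placebo to 500 mg. This implies AE rates of about 28, 42, 58 and 72%. The comparator is an exact trend test that conditions on each participant's AE total.

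| | Fisher | Within-participant trend |
|---|---|---|
| n = 9 | 19–22% | 44–48% |
| n = 18 | 47–53% | 81–84% |

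**5. How much comes from pairing and how much from dose order.** SD 2, AE rates 30/40/55/80%, scores equal to the dose in mg:

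| | Pooled Fisher | Pooled trend | Within-participant, any difference | Within-participant trend |
|---|---|---|---|---|
| n = 9 | 0.29 | 0.51 | 0.35 | 0.59 |
| n = 18 | 0.65 | 0.85 | 0.80 | 0.92 |

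Pairing alone adds 0.06 at n = 9 (0.35 − 0.29) and 0.15 at n = 18 (0.80 − 0.65). The rest of the gain needs the dose ordering.

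**6. Rare or threshold AEs (SD 2).**

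- Rates 2/5/10/25%, n = 9: Fisher 12–13%; within-participant trend 13% with equally spaced scores and 18% with mg scores; within-participant test of any difference 6%.
- Same rates, n = 18: Fisher 31–33%; trend 48–54%.
- AE confined to 500 mg (2/2/2/20%), equally spaced scores: 7.8% against 4.8% at n = 9, and 30.2% against 24.5% at n = 18, both in Fisher's favour.
- AE confined to 500 mg (2/2/2/40%), mg scores: 41% against 40% at n = 9, and 83% against 86% at n = 18.

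**The case against.** The best defence is that little depends on this p-value. Safety is secondary, n was chosen for pharmacokinetics, and no dose decision, stopping rule or safety margin refers to the test. All AEs are recorded whatever their cause (7.2). Under clustering the test errs towards too few rejections, so it raises no excess of false alarms. Looking for any difference rather than a trend is a legitimate choice. All of this stands, and it limits the severity.

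It could also be said that a statistical analysis plan would settle the method. But the Protocol has not left the matter open: it names a test, and that test does not fit its own design.

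Four stronger readings are tempting, and the documents do not support them.

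- A reader might infer that the p-values must be distorted. With no within-person correlation they are near nominal, and the Protocol gives no correlation.
- A reader might infer that power is always lost. Steps 5 and 6 show that it depends on AE frequency, dose pattern, score and sample size. Section 13.2 reports no side effects in earlier work apart from possible drowsiness, so the common-AE scenario may not be the relevant one.
- A reader might infer that a non-significant result will be reported as proof of safety. The Protocol nowhere says so.
- A reader might count the wide uncertainty after zero events against Fisher's test. The upper 95% limits, 1 − 0.025^(1/6) = 46% for 0 of 6 and 1 − 0.025^(1/12) = 26% for 0 of 12, come from the sample size and would be the same after any change of test.

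**Conclusion.** The point holds in this limited form. That the test in 11.2 does not match the crossover follows from the sequences alone and needs no assumption.

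The consequence is conditional. If AEs cluster within persons, the test is conservative: type I error is about 1 to 2.5% under an assumed logit SD of 1.5 to 3 with about 40% of exposures affected. For a common, graded AE it then has well under the power of a within-participant trend test, although part of that difference reflects the use of dose order. With rare AEs at n = 9, or an AE confined to the top dose, there is little or nothing to gain, and the trend test can do worse.

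If the same people entered both studies and the data were pooled, the dependence would be greater; the Protocol does not say whether they do. Severity: should-fix, for a secondary endpoint with no decision rule attached.

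**What to change.** Replace the Fisher sentence in 11.2 with two statements.

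1. For each treatment received, report the number and percentage of participants with any AE, with exact (Clopper-Pearson) 95% intervals. This alone would cure the fault, and p-values could then be dropped.
2. If a p-value is kept, obtain it from an exact test that permutes AE outcomes within participant. A dose-trend score is optional. If one is used, fix it in advance (equally spaced or in mg), since step 6 shows that the choice affects power.

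One condition should be stated with the test: permuting within a person assumes no period effect, and in the listed sequences 500 mg is never given in the first period.

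The cost is one paragraph and a few lines of code, with no new data, visits or participants. The downside is little or no gain in power when AEs are rare.
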